**Electroencephalography**

Electroencephalography (EEG) recordings will be conducted using a saline-soaked 32-channel EEG net, specifically designed for a quick and gel-free application. The EEG device is a CE marked and approved by University Hospitals Birmingham (UHB). The EEG measurements will be taken during the performance of cognitive paradigms, as well as during resting state. These recordings will provide valuable insights into brain activity patterns. The cognitive tasks performed during the EEG recordings will include the Attention Network Task, which has proven to be effective in studying attentional processes, and a versatile language comprehension paradigm. These tasks demonstrate sensitivity to age-related and early cognitive decline-associated changes in neural oscillations so are appropriate for maximizing sensitivity to intervention-related changes in older adults. The data from the EEG will be used to support mechanistic research into intervention related changes in neural oscillations in older adults. It will not be used to evaluate the safety or performance of the EEG device and it will not be used for diagnosis, monitoring or treatment guidance.

Stool sample collection

Stool samples will be collected in sterile containers. Participants will be provided with a sterile container and protective delivery bag to either post the sample directly to the research team or hand deliver to the hospital at the earliest convenience. Stool samples will be frozen at -80^o^C prior to analysis. Stool samples will be transferred for storage at the Department of Twins Research, King’s College London (our partners in a wider Wellcome Leap grant).

Venepuncture

Blood will be collected peripherally using BD vacutainers. A maximum of 70mL of blood will be taken at any one time. Blood samples will be used for eligibility, surveillance and further analysis. Eligibility and surveillance blood samples will be analysed for: full blood count, liver and renal function, vitamin B12 and metabolic acidosis. Surveillance bloods to be completed as per NICE guidelines. Samples will be prepared to enable further analysis and frozen at -80^o^C (this will include whole blood, peripheral blood mononuclear cells, serum, and plasma samples).

Adipose biopsies

Adipose tissue will be obtained from the abdomen. An aseptic technique will be used. Local anaesthetic will be infiltrated to the skin prior to biopsy. Biopsies should not be performed in participants taking anticoagulants or clopidogrel, but may be performed in participants taking only low dose aspirin 75mg.

Samples will be prepared to enable further analysis and frozen at -80^o^C and stored at the University of Birmingham.

Ultrasound quadriceps

Ultrasound measurement of quadriceps muscle will be performed using two-dimensional B-mode ultrasonography with a linear probe. Participants will be positioned in a semi-upright position with their knees resting at 10-20° using a firm wedge. Participants will be asked which leg they consider to be dominant and this will be recorded. Participants will be advised to relax their muscles. The distance from the greater trochanter to the lateral joint line of the knee will be recorded and a mark will be placed on the skin mid-way between the two points on both sides. All ultrasound measurements will be taken in line horizontally with these marks (37).

Muscle thickness measurements will be taken with the probe held in transverse position, perpendicular to the lateral border of the thigh (37). Contact gel will be applied to the skin. The depth will be adjusted until the femur and overlying structures are visible. The Rectus Femoris (RF) will be identified by locating its borders. The probe will be positioned such that the widest area of the RF appears over the midpoint of the femur. A frozen image at this location will be taken with the probe held in maximal relaxation. Thickness measurements of the subcutaneous tissues (SC), RF and Vastus Intermedius (VI) taken in a vertical line will be recorded, not including the fascia. Three frozen images will be used for all patients and a further image will be taken if there is greater than 10% variability between measurements. Frozen images taken which the research team deem to inappropriate due to showing unclear borders or grossly non-perpendicular imaging may be discounted from inclusion.

The mean of each reading will be used for analysis. BATT will be calculated as the total thickness of right VI + right RF + left VI + left RF. BATT: SC ratio (BATT-SCR) will be calculated as BATT divided by the total thickness of right SC + left SC (38). Where possible, the cross-sectional area of the right and left RF will be measured in the transverse plane (39). Each of these measurements will be repeated at both clinic visit with participants. All measurements will be performed by an investigator with training in taking these measurements. The intra-rater and inter-rater reliability of BATT has been previously shown to be excellent when using the same protocol (38). BATT will be used alongside walk speed and grip strength to diagnose sarcopenia (Appendix).

A further image will be taken with the probe held in the longitudinal position at each visit. Images will be saved and downloaded for assessment. Echogenicity will be determined using grey-scale analysis on Image J software (37, 38).

Bioelectrical Impedance Analysis

Bioelectrical impedance analysis (BIA) will be measured at each visit using the Bodystat Quadscan 4000. This procedure will not be performed if the participant has an implanted permanent pacemaker or defibrillator. The investigator will determine if a cardiac device is present by asking the participant and/or consultee where possible, reviewing medical notes, including imaging where appropriate, and externally examining the participant. Participants with cardiac devices may still be included in the study, but this procedure will not be performed. Two electrodes will be placed on the right foot; one below the base of the toes and the other on the ankle between the medial and lateral malleoli. Electrodes will be placed sideways so that the non-stick electrode connector is facing the researcher. The red alligator clip will be attached to the electrode nearest the toes and the black to the one at the ankle. A further two electrodes will be placed on the right hand; one behind the knuckles and the other on the wrist next to the ulnar head. The red alligator clip will be attached to the electrode nearest the fingers and the black to the one at the wrist. Height and weight measurements should be obtained (these can be extracted from clinical records if available or measured by the research team). During hospitalisation, weight may be estimated if it is not possible to obtain new readings, but this should be documented by the research team. Key participant information (height, weight, age, sex) will be entered onto the device and results will appear on screen. All returned results will be recorded. This will include fat weight, lean weight, total body weight, dry lean weight, skeletal muscle mass (SMM), and extracellular water (ECW) and intracellular water (ICW).

Three-day food record

Participants will be supplied with a three-day food record at their research appointments and asked to complete this for the next three days. They will then post this back to the research team. This will be used to estimate daily calorific and protein intake at each assessment, adjusted for the participant’s weight at that timepoint.

Adverse Event Reporting

Participants will be asked about any adverse events that occurred during the study period. These will be recorded and reported appropriately. During the telephone call mid-way through the study intervention period participants may be excluded from continuing in the study.

On day 7 all participants taking metformin will be rung and asked about side effects to the drug and to determine whether to withdraw the participant at this point or to increase the dose to the study dose of 1500mg for 21 days.

Drug Distribution

Participants will be supplied with the drugs they are taking for the study and counselled on possible side effects and the appropriate course of action. They will be supplied with all the drugs at the Day 0 Clinical Visit by a medical professional. The metformin will be prescribed by a study doctor and supplied by hospital pharmacy on the 2^nd^ research clinic visit. Spermidine and fisetin are nutraceuticals and therefore do not need a prescription. They will be supplied with instructions on how to take them.

Compliancy Pill Check

Participants will be asked to bring back the boxes and packets of the drugs they have been supplied with to check their adherence to the drugs during the study period. A member of the study team will check the boxes to see whether all the tablets have been taken. They will record the number of tablets left. They will also ask the participant if they took all their tablets as directed and if not why. The participants will also be asked to complete the drug record.

1. **REsilience and Frailty Research – Lived Experience of Community-dwelling Older AdulTs (REFLECT Study)**

8.1 Background

Older adults, particularly those living with frailty and from minoritised ethnic communities, remain under-represented in clinical research, limiting both the generalisability and equity of trial findings (52). Recruitment to REPROGRAM has been less diverse than anticipated, drawing mainly on the Birmingham 1000 Elders cohort and, more recently, on the NIHR *Be Part of Research* volunteer registry (53). This pattern mirrors wider challenges in enrolling older adults living with frailty into research and raises questions about how potential participants understand, experience and judge invitations to take part in frailty and geroprotector trials. Understanding these experiences is important for improving the inclusivity, acceptability and feasibility of future trials, consistent with NIHR INCLUDE guidance on under-served groups and MRC/NIHR guidance on complex interventions (52,59).

REFLECT is an optional qualitative interview sub-study nested within REPROGRAM. It focuses on the lived experience of community-dwelling older adults who have taken part in the trial.

8.2 Aims

The qualitative sub-study aims to:

1. Identify the practical, social, cultural and emotional factors – mapped to capability, opportunity and motivation – that make participation in frailty research easier or harder, including what stops people from taking part.
2. Identify the capability, opportunity and motivation factors that made participation in REPROGRAM easier or harder, including what nearly stopped people from taking part.
3. Generate participant-informed recommendations to improve invitation methods (including the use of NIHR *Be Part of Research* and Birmingham 1000 Elders), study information and trial procedures in future geroprotector and frailty trials.

8.3 Design and setting

REFLECT is a single-centre, qualitative interview study nested within REPROGRAM. Semi-structured interviews will be conducted with approximately 15–20 REPROGRAM participants. Purposive sampling will seek diversity in sex, age, intervention group, baseline frailty, ethnicity, recruitment route and socioeconomic circumstances, where feasible.

Interviews will follow best-practice guidance for qualitative interviewing in health and medical education, including careful preparation, piloting and iterative refinement of the topic guide with a PPI group, explicit attention to rapport and power dynamics, and planning for the management of emotional distress (54). Interviews will take place after the Day 28/35 post-intervention visit, in person, and within three months of V2, in the Inflammation Research Facility.

8.4 Participant identification, recruitment and consent

Eligibility for REFLECT is restricted to participants already enrolled in REPROGRAM who have completed the Day 28/35 post-intervention visit and retain capacity to consent. At the time of consent for the main REPROGRAM study, participants will be asked whether they are willing to be contacted about future optional sub-studies. This preference (yes/no) will be recorded on the updated main study informed consent form. Only participants who have agreed to further contact will be approached about REFLECT.

From this pool, the research team will use purposive sampling to achieve a maximum-variation sample. Eligible participants will be approached by the clinical research team by email, telephone or during the Day 28/35 visit and provided with a separate qualitative Participant Information Sheet describing the sub-study. They will normally be given at least 24 hours to consider participation before arrangements are confirmed. An additional £30 would be offered to REFLECT participants for their time.

Written informed consent for the qualitative interview will be obtained separately from consent for the main trial. Participants will be reminded that participation is voluntary, that they may decline to answer any question or stop the interview at any time, and that withdrawal from REFLECT will not affect their participation in REPROGRAM or their clinical care.

8.5 Data collection

Interviews will last approximately 45–60 minutes. Topic-guide domains will include:

- initial reactions to being approached about REPROGRAM (including recruitment route);
- understanding of the trial and geroprotector interventions;
- perceived risks, burdens and benefits;
- practical, social and emotional barriers and enablers to participation; and
- participants’ suggestions for improving information materials, recruitment strategies (including digital registries such as *Be Part of Research*) and study procedures (e.g. adipose biopsy, stool sampling, EEG).

Interviews will be audio-recorded using encrypted devices and transcribed verbatim. The interviewer will keep brief field notes on context, salient non-verbal cues and reflexive observations. If participants become distressed, the interview will be paused or stopped as appropriate. Participants will be offered time to recover, the option not to continue, and signposting to appropriate support if required. Any substantial distress will be documented and reported in line with Good Clinical Practice and sponsor requirements.

8.6 Sample size and information power

Rather than aiming for a fixed notion of “data saturation”, final sample size will be guided by the concept of information power (57). Approximately 12–20 interviews are expected to provide adequate information power given:

- focused study aims;
- a relatively specific clinical population (older adults enrolled in REPROGRAM);
- the use of a coherent theoretical framework (COM-B) (56); and
- an in-depth, iterative analytic strategy.

The final number will balance the richness and diversity of participants’ accounts with pragmatic considerations.

8.7 Data management and protection

Audio files will be transferred as soon as practicable after data collection to encrypted, password-protected University of Birmingham servers and deleted once checked transcripts are available. Transcripts will be pseudo-anonymised before analysis; names and other potentially identifying details will be removed or generalised. Documents linking participant identities to study identification numbers will be stored separately from qualitative data and accessible only to authorised members of the research team.

Qualitative data (transcripts, coding files and analytic memos) will be stored on secure institutional drives and/or within approved qualitative analysis software (e.g. NVivo), with access restricted to named study team members. Data will be archived for ten years in line with the wider REPROGRAM study and managed in accordance with Good Clinical Practice, the Data Protection Act 2018, UK GDPR and local NHS/University information-governance policies.

8.8 Data analysis

Interview transcripts will be analysed thematically using a reflexive thematic analysis approach (58). Analysis will proceed through iterative stages of:

- familiarisation with the data;
- generation of inductive codes capturing salient features of participants’ accounts;
- organisation of codes into candidate themes and sub-themes;
- review and refinement of themes against coded data and the full dataset; and
- production of an analytic narrative that addresses the study aims.

The COM-B model (Capability, Opportunity, Motivation–Behaviour) will be used as a sensitising framework to explore how cognitive, physical, social and emotional factors shape decisions about research participation (56). A case-by-theme matrix will be developed to support systematic comparison within and across participants, drawing on principles from the Framework Method (55). To enhance reflexivity and credibility, a subset of transcripts will be independently read and coded by more than one member of the research team, with regular analytic discussions to review interpretations, consider alternative explanations and reflect on researcher positionality. Qualitative data management and coding will be supported by NVivo.

8.9 Outputs, dissemination and integration with the main trial

Findings from REFLECT will inform at least one peer-reviewed manuscript describing older adults’ motivations for participation, perceptions of study procedures (for example adipose biopsy, stool sampling and EEG), tolerability of the interventions, and views on the future use of geroprotectors in clinical care. Qualitative insights will also be integrated, where appropriate, into mixed-methods outputs from REPROGRAM to contextualise and interpret the biological and mechanistic findings and to guide optimisation of recruitment strategies, information materials and trial procedures in future geroprotector and frailty trials, in line with NIHR INCLUDE and MRC/NIHR guidance (52,59). Key qualitative themes will be summarised in accessible language within participant result summaries and public-engagement activities, with input from the PPI group to ensure clarity and relevance.

1. Detailed laboratory methodology for mechanistic studies

Laboratory based assays will be conducted at University of Birmingham, stool microbiome and metagenomics which will be conducted at the Department of Twins Research King’s College London. We may send samples to our research partners for analysis that cannot be completed at University of Birmingham or Kings College London. They will not have access to personal data. Analysis of the data will be conducted at the University of Birmingham.

Stool microbiome and metagenomics

Dysbiosis is a hallmark of ageing that influences health (41). Microbial composition and functional potential will be assessed through metagenomics in stool to identify biomarkers of resilience using state of the art metagenomic sequencing (Illumina NovaSeq6000 DX sequencer). This will include bacterial taxonomic and functional profiling, and virus profiling (42). This will allow assessment of the changes of the gut microbiome following the intervention with either metformin, spermidine or fisetin. This is considered particularly important given the known effect of metformin on gastrointestinal tract with diarrhoea being a commonly reported side effect ((Relative risk=2.445 95%CI [1.656, 3.609], p=0.0001) compared to controls.)

DNA methylation, immune system ageing, compromised autophagy, mitochondrial function, nutrient sensing and stem cell exhaustion

Epigenetic age and epigenetic response (at days 0, 30 and 90) will be assessed from isolated whole blood DNA using the Illumina EPIC array and published algorithms **(43)**. Immunesenescence will be assessed by deriving the IMM-AGE score **(36)** by immunostaining and flow cytometry analysis of isolated PBMCs identifying 8 immune cell types (total T cells, naive CD4 T cells, effector memory CD4 and CD8 T cells, EMRA CD8 T cells, CD28− CD8 T cells, CD57+ CD8 T cells and regulatory T cells). Epigenetic age and immunesenescence are associated with risk of morbidity and mortality. Immunesenescence has been shown in mice to be a key driver of frailty **(44)** and in humans to predict impaired resilience in patients following traumatic injury **(45)**. Autophagic flux assessed by LC3-II breakdown by flow cytometry will determine compromised autophagy from whole blood **(46)**. T cells will be assessed for mTOR activation (by phosphoflow cytometry) and mitochondrial function (measuring cellular energetics using a Seahorse system) as further hallmarks of ageing. Stem cell exhaustion, a hallmark of ageing, will be assessed in mesenchymal stem cells (MSCs) isolated from peripheral blood, to evaluate multipotency, senescence and metabolic plasticity.

Adipose tissue to assess cellular senescence and tissue-based resilience biomarkers

Transcriptomics analysis (bulk RNAseq), will allow assessment of senescent cell burden using the SenMayo analysis (47). This will be used to identify associations between dynamic resilience and canonical signalling pathways that mediate muscle mass and myogenesis (Ingenuity Pathway Analysis) and adipogenesis linked with dynamic resilience or progression of frailty. Protein coding and non-coding RNAs associated with resilience will also be assessed. Primary adipose-derived stem cells (ADSC will be isolated from a third of the tissue and assessed immediately for autophagic flux and mitochondrial function or frozen for later use. The remaining snap frozen tissue will be analysed histologically to confirm the presence of senescent cells (Lamin B1, SA-β-Gal, TAF) and lipid accumulation (e.g., Oil Red O staining).

Inflammatory and senescence markers

Analysis of frozen serum using ELISA and multiplex technology will allow assessment of systemic inflammatory and senescence markers.

1. Safety reporting

An adverse event (AE) is any untoward medical event affecting a clinical study participant. Each initial AE will be considered for severity, causality or expectedness and may be reclassified as a serious event or reaction based on prevailing circumstances.

An adverse reaction (AR) is where it is suspected that an AE has been caused by a reaction to the study supplement

A serious adverse event (SAE), serious adverse reaction (SAR) is any AE, AR or UAR (unexplained adverse reaction) that at any dose:

• results in death

• is life threatening

• requires hospitalisation or prolongation of existing hospitalisation

• results in persistent or significant disability or incapacity

• is a congenital anomaly or birth defect

• Or is otherwise considered serious

Note: Hospitalisations for treatment planned prior to consent and hospitalisation for elective treatment of a pre-existing condition will not be considered as an SAE. However, any adverse events occurring during such hospitalisation will be recorded. Adverse events, adverse reactions and serious adverse events will be reported by participants or other health care professionals.

All AEs and SAEs will be recorded from the time a participant consents to join the study until the last sstudy visit. Participants with unresolved AEs at the last study visit will be followed up until resolution or 30 days after last visit of that participant, whichever is sooner.

The CI, or delegate will ask about the occurrence of AEs and hospitalisations at the second study visit (day 28/35). AEs will be recorded on the AE Log in the CRF. SAEs will be submitted on an SAE form to the Chief Investigator and study team within 24 hours of becoming aware of the SAE. SAEs will be assessed for expectedness and causality by the Investigator. The Sponsor will be informed of any reportable SAEs. The evaluation of expectedness will be made based on the knowledge of the reaction and the relevant product information.

1. Ethical and regulatory considerations

Assessment and management of risk

Physical risks

*Burden of time*

Burden of time is subjective and will vary between participants. Participants will be given time to complete the assessments and to ensure they do not feel rushed, whilst also reassuring them that they can stop or withdraw at any time.

*Burden of completing tasks*

Some participants might find completion of the SPPB and other assessments particularly burdensome, due to fatigue. Participants will be given sufficient time and opportunity to complete these tasks. Where participants were unable to complete tasks, this will be recorded along with the reason for being unable to do so.

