| Stool collection | X |  |  |  | X |  |
| EEG | X |  |  |  | X |  |
| Venepuncture | X | X |  |  | X |  |
| Adipose biopsies |  | X |  |  | X |  |
| Adverse event reporting | X | X | X | X | X |  |
| Drug distribution |  | X |  |  |  |  |
| Compliancy pill count |  |  |  |  | X |  |
| Qualitative Interview |  |  |  |  |  | X |

Co-morbidities and medications

Co-morbidities and medications will be recorded using check boxes for frequently encountered conditions and medications with the option for free text to record less common co-morbidities and medications.

Handgrip strength

Handgrip strength will be measured using a handheld dynamometer (Jamar, Takei Grip D, or other calibrated device). Where the participant can sit out in a chair, handgrip strength will be measured with the arm flexed at 90^O^ at the elbow and the forearm supinated. If the participant cannot sit out and measurements are taken in the bed, this will be recorded and measurements will instead be performed in the most upright position that is feasible. Participants will be asked to “squeeze as hard as [they] can”. Handgrip strength will be measured twice on each side and the best recording of all will be used for analysis (29).

Short physical performance battery

The Short Physical Performance Battery (SPPB) is a standardised measure of physical performance that has been shown to be sensitive to change and provides an objective measure of physical function (30). SPPB consists of usual gait speed, side-by-side stand, semi-tandem stand, tandem stand, and five chair stands. A total score of 12 is derived, with a lower score representing reduced physical performance. SPPB will be measured within 48 hours of admission and 48 hours of discharge. Gait speed will be measured by asking the participants to walk a four-metre course at their “usual pace”. Participants will be asked to complete five chair stands “as quickly as [they] can” (see Appendix). If it is not possible to measure gait speed or any part of the SPPB at any planned visit the reasons for this will be recorded (e.g., if either the investigator or the participant considers it unsafe to do so). The need or use of a mobility aid will be recorded. It is recommended that the SPPB should be performed after assessment of muscle quantity/quality (ultrasound quadriceps and bioelectrical impedance analysis), to ensure that these assessments are not affected the effect of exercise.

Activities of Daily Living (ADL) assessment

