#### Adipose biopsies

The risks of these procedure are pain, infection, bleeding and local nerve damage (rare). Pain following the procedure will be minimised by using local anaesthetic and advising participants to take simple analgesia such as paracetamol afterwards. Aseptic technique using a sterile field and gloves will be used to minimise the risk of infection. The procedure will not be performed on participants who are taking anticoagulants or clopidogrel, or who have a known bleeding disorder.

*Medical Emergencies*

The Clinical Visits will all occur at the Clinical Research Facility at the University of Birmingham which is located within the Queen Elizabeth Hospital Birmingham. Staff are trained in the recognition and management of medical emergencies and there are procedures in place to manage medical emergencies which may take place during any study or study visit. If required the management of an unwell participant can be escalated to include the NHS medical crash team and a participant can be transferred to an NHS location in the Queen Elizabeth Hospital Birmingham for further assessment and management.

*Electroencephalography*

The risks associated with the saline-based EEG are minimal. Participants may find the task-based EEG slightly tedious due to its repetitive nature, but no significant discomfort is expected.

Diagnosis of previously unknown conditions

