**Table 3 - Assessment and management of risk**

| **Intervention** | **Risks** | **Amelioration of Risk** |
| --- | --- | --- |
| Metformin MR | **Side effects as listed in British National Formulary (BNF)**  **Common or very common**  Abdominal pain; appetite decreased; diarrhoea; gastrointestinal disorder; nausea; taste altered; vitamin B12 deficiency; vomiting  **Rare or very rare**  Hepatitis; lactic acidosis (discontinue); skin reactions | Metformin MR will be started at a low dose of 500mg once a day as advised by BNF. This will reduce the risk of gastrointestinal side effects.  Participants with a diagnosis of symptomatic heart failure will be excluded to reduce the risk of lactic acidosis.  Vitamin B12 levels will be checked prior to commencing the drug intervention and following completion of the study to diagnose deficiency. Participants with a deficiency prior to starting will be excluded from participation.  Surveillance blood tests will be checked one week after discontinuing metformin MR to ensure there has been no impact on liver function. |
| Spermidine | No known side effects | Surveillance blood tests will be checked one week after discontinuing spermidine to ensure there has been no impact on organ function |
| Fisetin | No known side effects | Surveillance blood tests will be checked one week after discontinuing fisetin to ensure there has been no impact on organ function. |

Research Ethics Committee (REC) and other Regulatory review & reports

Before the start of the study, a favourable opinion will be sought from a REC (Research Ethics Committee) and the Health Research Authority (HRA) through the National Research Ethics Service for the study protocol, informed consent forms and other relevant documents. All correspondence with the REC will be retained. It is the Chief Investigator’s responsibility to produce the annual reports as required. The Chief Investigator will notify the REC of the end of the study. An annual progress report (APR) will be submitted to the REC within 30 days of the anniversary date on which the favourable opinion was given, and annually until the study is declared ended. If the study is ended prematurely, the Chief Investigator will notify the REC, including the reasons for the premature termination. Within one year after the end of the study, the Chief Investigator will submit a final report with the results, including any publications/abstracts, to the REC.

Regulatory Review & Compliance

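### Complications of the second adipose biopsy that first appear after the Day 28/35 visit have no planned recording, because new adverse-event recording stops at that visit

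*Protocol*

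**What the plan says.** The Safety reporting section (section 10) sets the window for adverse events (AEs) and serious adverse events (SAEs): "All AEs and SAEs will be recorded from the time a participant consents to join the study until the last sstudy visit". It then adds a tail: "Participants with unresolved AEs at the last study visit will be followed up until resolution or 30 days after last visit of that participant", whichever comes sooner. That tail applies to people who already have an open event when they attend.

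Table 2 (Study procedures) gives two biopsies per participant, at Day 0 and at the post-intervention assessment on Day 28/35: "Adipose biopsies | | X | | | X". AE reporting is ticked at the initial assessment, Day 0, the Day 7 call (metformin only), the Day 10/17 call and Day 28/35: "Adverse event reporting | X | X | X | X | X". Its cell under the qualitative interview is empty.

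On the procedure itself, the Adipose biopsies paragraph in section 11 says: "The risks of these procedure are pain, infection, bleeding and local nerve damage (rare").

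On laboratory safety, Table 3 says for metformin: "Surveillance blood tests will be checked one week after discontinuing metformin MR to ensure there has been no impact on liver function". It has equivalent entries on organ function for spermidine and fisetin.

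**The concern.** Recording of new events closes on the day of an invasive procedure done for research in volunteers aged 70 or over. Of the four risks the protocol names, infection, later bleeding and nerve symptoms can all first show after the participant has left. The 30-day tail does not catch them, because they are not yet present, and so not unresolved, at the visit. No later contact asks about them.

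The two biopsies in the same person are therefore observed very unequally. The events that would be missed belong to a procedure that every participant who completes the study undergoes a second time, and any complication rate per biopsy drawn from the AE log would lean low.

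The same visit also supplies the final surveillance bloods, which Table 3 offers as the check on organ function. The protocol does not say whether an abnormal result returned after the visit is entered as an AE.

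**Working it through.** **Inputs**
- Participants starting treatment: 60 (Recruitment target).
- Biopsies: Day 0 and Day 28/35 (Table 2), with a +3 day allowance on the latter.
- Treatment length: metformin 7 + 21 days; spermidine and fisetin 21 days (Table 1).
- Final bloods: one week after the last dose (Table 3).
- New-event window: consent to last visit (section 10).

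**Step 1: reproduce the last-visit day.** Treatment length plus 7 days:
- metformin: 7 + 21 + 7 = Day 35
- spermidine, fisetin: 21 + 7 = Day 28

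This matches the Day 28/35 visit and the five-week follow-up in the Study summary. The final bloods, second biopsy and last AE contact fall at one visit.

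**Step 2: is there a later contact?** Only the optional REFLECT interview, for about 15 to 20 of the 60 participants, with an empty AE cell in Table 2. The laboratory section mentions a day 90 time point for epigenetic response, but Table 2 has no such visit.

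**Step 3: biopsies affected.**
- Planned: 60 × 2 = 120, of which 60 are at the last visit; 60/120 = 50%.
- Assuming 1 in 10 participants drops out before the last visit (the sample-size section recruits 10 per sex where 9 are needed): 54/(60 + 54) = 54/114 = 47%.

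**Step 4: recording time for new events after each biopsy.**

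| Biopsy | Spermidine, fisetin | Metformin |
| --- | --- | --- |
| First (Day 0) | 28 to 31 days | 35 to 38 days |
| Second (Day 28/35) | rest of the visit | rest of the visit |

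**Step 5: effect on a per-biopsy complication rate.** Let p be the complication risk, equal at both biopsies, and f the fraction of complications that first appear after the visit. Assume all first-biopsy complications are captured.
- Expected events: 120p
- Expected recorded events: 60p + 60p(1 − f) = 120p − 60pf
- Relative shortfall: 60pf / 120p = 0.5f

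| Late-onset fraction f | Shortfall |
| --- | --- |
| 0 | 0% |
| 0.25 | 12.5% |
| 0.5 | 25% |
| 1 | 50% |

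The documents give no value for f, so only the range 0 to 50% can be stated.

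**Step 6: bloods.** The sample is taken at Day 28/35, inside the window. An abnormal value describes the participant on that date and can be logged as an event unresolved at the last visit. Section 10 does not exclude this. Section 11 has significant findings explained to the participant and passed to the GP or medical team, but does not say they are recorded as AEs. The protocol gives no laboratory turnaround time.

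**The case against.** **The window serves its main purpose.** Recording runs for a week after the last dose in every group, so ascertainment of drug effects is not cut short. This stands: the gap concerns a procedure, not the interventions.

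**Biopsy complication rates are not a trial outcome.** True. The 60 first biopsies also have at least four weeks of recording, so a rate per first biopsy can still be estimated. This limits the statistical consequence. It does not remove the gap in safety recording after the second procedure.

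**Participants and clinicians can report events themselves.** Section 10 does allow for this, but the stated recording period has ended by then and nobody is scheduled to ask.

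Three stronger readings are tempting and are not supported:
- A reader might infer that all complications of half the biopsies are lost, or that a complication rate is understated by half. Pain or bleeding evident at the visit is inside the window and, if unresolved, is followed for up to 30 days. A shortfall of 50% would require every complication to appear late.
- A reader might infer that abnormal final bloods cannot count as AEs. The protocol is silent on results returned later; it does not exclude them.
- A reader might take the safety section to contradict Table 2 on when events are asked about, since it says "The CI, or delegate will ask about the occurrence of AEs and hospitalisations at the second study visit (day 28/35"). It does not say that this is the only occasion, and it records all events from consent. What remains is mainly a labelling slip: Day 28/35 is called the second visit there and V2 in section 8.3, whereas Drug Distribution uses the 2nd clinic visit for Day 0.

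**Conclusion.** The point holds in a limited form. As written, late-onset complications of the second adipose biopsy have no planned recording, and no other part of the protocol repairs this. It applies to 60 of 120 planned biopsies (about 47% of those performed under the 10% dropout assumption). The understatement of a per-biopsy complication rate is 0.5 times the late-onset fraction, so between 0 and 50%, assuming equal risk at both biopsies and full capture after the first.

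For the final bloods, the finding is only that recording of results returned after the visit is unspecified. This is an inexpensive improvement to safety ascertainment. It does not undermine the primary outcome or the drug-safety data.

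**What to change.** 1. In section 10, extend recording of new AEs and SAEs to 30 days after the participant's last visit, using the limit already stated there for unresolved events.
2. Add one AE phone contact after the second biopsy as a new column in Table 2.
3. State that clinically significant changes from baseline in the Day 28/35 bloods, as judged by the investigator, are recorded as AEs dated to that visit whenever the laboratory reports them. The reference to baseline matters because the eligibility criteria admit people with some renal or liver-test abnormality, and unchanged values should not be logged as new events.
4. Reconcile the visit label in section 10 with Table 2: list the AE contacts as Table 2 has them and use one numbering for the visits throughout.

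Cost: one short call per participant (at most 60) and a protocol amendment. No new procedure is needed. The five-week follow-up in the Study summary, and the end-of-study definition as the last participant's last visit, should be checked against the added contact.
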